**JHM IRB - eForm A – Protocol**

- **Use the section headings to write the JHM IRB eForm A, inserting the appropriate material in each. If a section is not applicable, leave heading in and insert N/A.**
- **When submitting JHM IRB eForm A (new or revised), enter the date submitted to the field at the top of JHM IRB eForm A.**

***************************************************************************************************

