**Personalized Treatment Planning for Radioiodine Therapy of Thyroid Disease**

**Protocol Version 1.0, dated December 17, 2017**

1. **Abstract**

The Collar Therapy Indicator (CoTI), a device placed in cloth collar around the neck resembling a turtle neck sweater collar with a connecting wire and recording box (Fig. 1), has been shown in a single small previously published experience to provide data regarding radioiodine exposure that correlates with conventional methods of measuring I-123 and I-131 uptakes after diagnostic dose administration and/or therapy for thyroid disorders . We hypothesize that the device’s continuous measurement capability will permit more accurate estimates of radiation exposure to thyroid tissue than conventionally employed methods assessing fractional uptake at one or a few time points. It may also provide information about the extent of variability in the absorbed radiation dose among patients with thyroid cancer and hyperthyroidism. By providing more complete information about individual patient’s exposures, it will facilitate more accurate estimation of the administered I-131 dose requirements for both control of hyperthyroidism and thyroid remnant ablation while reducing the need for repeated visits to the clinic for dosimetry measurements. The aims of our project include the following: (1) Compare quantitative imaging-derived thyroid time activity curve to that obtained using the CoTI and to determine the extent to which there is variability in radiation dose predicted using conventional methods to that predicted from measurement of the full Time-Activity Curve (TAC); (2) Evaluate the uptake and clearance kinetics across the 5 patients in each category as proof of principle for a potential larger trial to investigate use of this device in optimizing the administered doses of radioactive iodine to achieve therapeutic goals while minimizing risks of comorbidities, such a post-radioiodine hypothyroidism in patients with Graves disease. (3) Evaluate patient experience, convenience, and discomfort in using the CoTI device with a survey instrument.

1. **Objectives** (include all primary and secondary objectives)

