## Primary Objective;

To perform a pilot (exploratory) study using a novel AG Medical Collar Therapy Indicator (CoTI) to evaluate the variability in radioiodine kinetics across patients treated for hyperthyroid Graves disease and postoperative thyroid remnant ablation for thyroid cancer.

- - For Graves disease, after administration of 0.2 mci I-123 and low dose (200 µCi) I-131, to compare conventional 6, 24, 48 and 72-hour fractional thyroidal radioiodine uptakes with single photon emission (with low-dose computed tomography [SPECT/CT] for quantification and attenuation correction) with the activity measured continuously by the COTI device, which is placed in collar around the neck resembling a turtle neck sweater collar with a wire and recording box.
  - For remnant ablation, after therapeutic administration of 30 mCi I-131, to compare conventional 24, 48, 72 hr. and 7-day SPECT (with low dose CT for quantification and attenuation correction performed at 24, 48, 72 hours and 7 days) with the activity continuously measured by the COTI device, as described above.

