**Secondary Objectives;**

## To validate use of the cervical collar device as an enhancement for quantitative measurement of thyroid uptake in patients after diagnostic I-123 and low dose I-131 in Graves disease

## To validate use of the cervical collar device as an enhancement for quantitative measurement of thyroid uptake in patients after therapeutic I-131 for thyroid remnant ablation in thyroid cancer.

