**No non-FDA drugs will be administered. The CT scans are expected to be without iodinated contrast agents.**

Date: ____________________

Principal Investigator: _________________

Application Number: ___________

1. **Study Statistics**
2. Primary outcome variable.
3. Secondary outcome variables.
4. Statistical plan including sample size justification and interim data analysis.

This is a pilot study involving 10 patients and hence there are no interim data analysis or conflicts regarding sample size. Descriptive data will be outlined for all the participants tabulating the variables as determined. The intrapatient variability as well as accuracy and precision of the device will be obtained individually for Group I and Group II patients. The correlation (non-parametric) Spearman correlation coefficient will be obtained to assess the relationship between the uptake and findings as obtained by the collar device and conventional methods of uptake measurement.

1. Early stopping rules.

Early Stopping Rules Include but not limited to:

1. Severe, unexplained discomfort with the device. (2) Lack of device tolerability or interference with optimal functioning of daily activity (3) Discomfort after stopping anti-thyroid treatments causing rebound hyperthyrodism
2. **Risks**
3. Medical risks, listing all procedures, their major and minor risks and expected frequency. b Steps taken to minimize the risks.

The following risks are anticipated:

• Pressure sensation and possible skin irritation due to compression of skin around the neck. The patients can remove the collar for a few hours every day to avoid this.

• Transient redness around the neck if the collar is placed too tightly.

• For persons with prior thyroid surgery, the device might give cause an unpleasant rubbing sensation, especially if the surgical scar is very fresh.

• Rarely, it could cause patients to experience discomfort with swallowing, but the patients will be given all the necessary information to prevent this. If the participants feels uncomfortable, he/she can remove the device anytime

• The participants will also receive 1-4 low-dose CT scans. The cumulative radiation doses will be very low. Radiation imposed minimal risk at very low doses.

- The participants will undergo a low dose 0.2 mci I-131 dosing that is not associated with thyroid “stunning” and is much less than the 12 mCI (about 60 times 0.2) that they will receive for theraupetic treatment of graves disease

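### No outcome variable is named, yet two objectives promise to validate the collar from five patients per group with a rank correlation

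*Protocol*

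**What the plan says.** The Study Statistics section prints "Primary outcome variable" and "Secondary outcome variables" as consecutive headings with nothing under either, then moves to the statistical plan. The form's own instruction is "If a section is not applicable, leave heading in and insert N/A"; no such entry was made.

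The statistical plan says "This is a pilot study involving 10 patients and hence there are no interim data analysis or conflicts regarding sample size". It then promises descriptive tables, intrapatient variability, and accuracy and precision of the device by group, with no metric for the last two. Its one named statistic is a Spearman correlation "to assess the relationship between the uptake and findings as obtained by the collar device and conventional methods of uptake measurement".

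The Primary Objective is "to evaluate the variability in radioiodine kinetics across patients treated for hyperthyroid Graves disease" and after remnant ablation. Under it stand collar-versus-conventional comparisons at four times in each disease group, none singled out. Aim 1 in the Abstract adds the full time-activity curve and the predicted radiation dose.

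The Secondary Objectives include "To validate use of the cervical collar device as an enhancement for quantitative measurement of thyroid uptake in patients after therapeutic I-131" and a parallel objective for Graves disease. Neither states what result would count as validation.

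**The concern.** Naming the primary outcome is the protocol's job, and this form asks for it by heading, so a separate SAP would not remove the point. With the heading empty, whichever time point, isotope or summary looks best can become the headline once the data are seen.

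The validation objectives raise the stakes. A favourable coefficient is the natural evidence to offer for them, but Spearman's coefficient uses only the ordering of patients. A collar that read wrong by a constant factor in every patient would still score 1.0. Even a coefficient fixed in advance would therefore not show that the collar measures uptake correctly, and five patients leave its value almost undetermined.

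**Working it through.** The protocol states no alpha, power, margin or sample-size formula, so there is no figure of its own to reproduce. The 0.9 cut-off below is an assumption, used only for illustration.

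**1. How many coefficients the schedule permits** (Scheduled Imaging times and Tables A to C)

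| Block | Reference | Paired times | Pairs |
|---|---|---|---|
| Group I(A), I-123 | probe | 6 and 24 h, plus 0 h if the background reading is counted | 2–3 |
| Group I(B), I-131 | SPECT | 6, 24, 48, 72 h (the 96 h collar reading has no SPECT) | 4 |
| Group II, I-131 | SPECT | 24, 48, 72 h, day 7 (the text's collar list omits 72 h; Table C includes it) | 3–4 |

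Total: 2+4+3 = 9 to 3+4+4 = 11. Probe uptake entries in Table B could add up to two more. Study Procedures gives five patients per group. It is not stated whether the same five Graves patients pass through both I(A) and I(B); if they are split, n per coefficient is below five.

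**2. Exact null distribution at n = 5.** There are 5! = 120 equally likely rank orders. With rho = 1 − 6Σd²/(5×24), five of them give rho ≥ 0.9, so P = 5/120 = 4.2%.

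**3. At least one favourable value among k independent coefficients:** 1 − (1 − 5/120)^k.

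- k = 1: 4.2%
- k = 2 (one named per disease group): 8.2%
- k = 9: 31.8%
- k = 10: 34.7%
- k = 11: 37.4%

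**4. Allowing for correlation between times.** Readings in one patient at successive times are not independent. Simulating ten coefficients in blocks of 2, 4 and 4 with no true association (60,000 trials per setting), the chance of at least one rho ≥ 0.9 was:

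| Within-patient correlation across times | Chance |
|---|---|
| 0 | 35% |
| 0.5 | 34% |
| 0.8 | 31% |
| 0.9 | 28% |

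At 0.95, a separate run of 40,000 trials gave 25%.

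**5. Precision of one observed value.** For rho = 0.9 and n = 5, on the Fisher scale: atanh(0.9) = 1.472; SE = √(1.06/2) = 0.728; 1.472 ± 1.96 × 0.728 = 0.045 to 2.899. Back-transformed, this is 0.05 to 0.99. With SE = √(1/2) the lower limit is 0.09; with the Bonett–Wright SE it is −0.17. All three are rough at this sample size and agree that the coefficient is barely constrained.

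**The case against.** The best defence is that this is a ten-patient pilot and says so repeatedly: in the Primary Objective, Study Procedures, the blinding statement, the device rationale and the statistical plan. It plans no test, promises descriptive data for all participants, and does not let the collar drive therapeutic dosing. Accuracy and precision are planned too, so correlation is not the only intended evidence. All of this stands, and it limits the point to selective reporting. It does not fill the empty headings, supply a metric for accuracy and precision, or reconcile a pilot with objectives worded as validation.

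A reader might infer more than the protocol supports:

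- *That ten analyses are planned.* The plan speaks of one coefficient and leaves the number open. Pooling repeated readings is equally permitted.
- *That the chance of a misleading result is 58%.* That figure counts |rho| ≥ 0.9 among ten and so includes strongly negative values, which nobody could present as validation.
- *That the best and worst coefficients will usually contradict each other.* This depends on the assumed true correlation. With 0.7, ten coefficients include both a value ≥ 0.9 and a value ≤ 0.5 in about 93% of trials (81% at within-patient correlation 0.9). With 0.9 the figure is about 54–67%, and with 0.95 about 30–36%. The protocol gives no basis for choosing among these.
- *That the go-ahead for a larger trial hangs on a Spearman value.* Aim 2 in the Abstract offers the uptake and clearance kinetics "as proof of principle for a potential larger trial to investigate use of this device"; it does not mention the correlation.

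**Conclusion.** The point holds in limited form. No outcome variable is named anywhere. About 9 to 11 collar-versus-reference coefficients are open to choice, each on at most five patients. Two objectives claim validation without a criterion, although the only named statistic cannot show agreement. The design cannot support the word *validated* in either group.

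The size is illustrative: about 28–35% for at least one rho ≥ 0.9 among ten when there is no association, against 4.2% for one named coefficient. This assumes five patients per coefficient, a cut-off of 0.9 and within-patient correlation across times between 0 and 0.9. Since no alpha or test is stated, it should not be read as an inflated type I error rate. The gap does not stop the pilot from running; it should be closed before the collar data are analysed.

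**What to change.** 1. **Name the collar-comparison outcome.** Prespecify one agreement measure per I-131 group, built from readings at the shared SPECT times. One workable choice is the per-patient ratio of the collar to the SPECT time-integrated curve, each divided by its own 24 h reading, over 6–72 h in Graves disease and 24 h to day 7 in cancer. State the integration rule and treat physical decay alike in both curves. Report every individual ratio with the geometric mean and 95% interval, alongside the between-patient variability in kinetics that the Primary Objective names.

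   This form needs no absolute calibration. That matters because the collar output is in counts per second and the phantom appears only within the background measurements. Use an absolute activity ratio only if a collar calibration is specified. The 72 h collar reading for Group II must first be reconciled between the text and Table C.

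2. **Fill the secondary heading.** List the time-point correlations, the I-123 comparison and the survey as exploratory, all to be reported and none with a significance claim. Name a metric for accuracy and for precision.

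3. **Reword both validation objectives** to: *To obtain preliminary estimates of the performance of* the collar. State that validation is left to a larger trial.

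The cost is a short wording amendment and one derived quantity per patient, with no added patients, scans or visits. The pilot gives up a single-time-point headline and any validation claim, and the normalised ratio tests the shape of the curve, not its absolute level.

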## To obtain detailed early-phase thyroid uptake data using a cervical collar device in the Graves disease and thyroid cancer patients as described above.

1. **Background**

Radioiodine treatment for thyroid disorders represented an early example of individualized medicine. Since its introduction 80 years ago, the therapeutic I-131 dosage has usually been tailored to individual patient requirements based on the uptake of a tracer radioiodine dose . Various techniques have been employed to estimate the administered dose of I-131 for optimal therapeutic benefit . Estimated exposure has typically been extrapolated from the results of activity measurements at one or two time points, e.g., at 4 and 24 hours . We now know that treatment of hyperthyroid Graves disease with these methods lead to a 13-25% rate of failure to cure hyperthyroidism and a 46-80% rate of long-term hypothyroidism in cured patients . Similarly, such relatively crude dosimetry doubtless result in significant overtreatment in the case of remnant ablation for differentiated thyroid cancer.For patients with differentiated thyroid cancer requiring remnant ablation, the administered activity has, in most cases, been derived empirically, ranging between 30-100 mci . The high success rates in ablating remnant thyroid tissue implies that many patients are still treated with higher 131-I doses than required, with potential side effects, such as radiation sialadenitis.

1. **Study Procedures**

This will be an unmasked prospective pilot study involving patients with Graves disease (Group I) and differentiated thyroid cancer (Group II). Five patients in each group will have radiation activity measurements using the COTI devise. All persons in the study will receive 131-I treatment based on the current standards of care for dose estimation.

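### Accuracy and precision are promised without an estimator, and the only named collar-to-reference method, a Spearman correlation, cannot measure agreement

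*Protocol*

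**What the plan says.** The aims are quantitative. The protocol's Abstract, aim (1), is to "Compare quantitative imaging-derived thyroid time activity curve to that obtained using the CoTI", and also "to determine the extent to which there is variability in radiation dose predicted using conventional methods" compared with that from the full time-activity curve. Two of the Secondary Objectives begin "To validate use of the cervical collar device as an enhancement for quantitative measurement of thyroid uptake", one for Graves disease and one for remnant ablation.

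The analysis is in Study Statistics. It starts from a sample of ten ("This is a pilot study involving 10 patients and hence there are no interim data analysis or conflicts regarding sample size"), and Study Procedures splits this evenly: "Five patients in each group will have radiation activity measurements using the COTI devise". After descriptive tables it says "The intrapatient variability as well as accuracy and precision of the device will be obtained individually for Group I and Group II patients". The next sentence names the method: a "Spearman correlation coefficient will be obtained to assess the relationship between the uptake and findings as obtained by the collar device" and by conventional uptake measurement. It does not say whether the coefficient is computed within each patient, over all patient-times pooled, or across patients at one time.

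The two sides are on different scales. Under Study Device the collar reads counts per second. The reference is fractional uptake by probe in Group I(A) and SPECT in Groups I(B) and II.

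**The concern.** Whether the collar gives the right activity, the right clearance and hence the right integrated exposure is a question of agreement. A Spearman coefficient asks only whether two sets of readings fall in the same order. A collar that reads half or twice the true activity, or clears at the wrong rate, can keep the order intact.

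The open unit of analysis adds a second problem. Within a patient there are only three or four pairs, and their order is driven largely by time since dosing. If patient-times are pooled, repeated readings are treated as independent and the common time course contributes correlation of its own.

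The study is described as proof of principle for a possible larger trial on optimizing administered activity. A high rho reported under the heading of validation could carry an unnoticed error of scale or half-life into that trial.

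**Working it through.** The ten patients come from no formula, so there is no planned figure to reproduce. The check concerns how the named statistic behaves at the protocol's own sampling times.

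**Paired times (Scheduled Imaging times; Tables A–C).**
- Group I(A): collar and probe at 0, 6 and 24 h, so 3 pairs, of which 0 h is a background reading.
- Group I(B): SPECT at 6, 24, 48 and 72 h. The collar is also read at 96 h, without SPECT, so 4 pairs.
- Group II: SPECT at 24, 48, 72 h and day 7. The text lists collar readings at 24, 48, 96 h and day 7 (3 pairs); Table C also shows a 72 h reading (4 pairs).

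**1. Within one Group II patient.** Assume mono-exponential curves with equal starting values: reference half-life 72 h, collar 144 h.

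| Time (h) | Reference, 2^(−t/72) | Collar, 2^(−t/144) |
|---|---|---|
| 24 | 0.794 | 0.891 |
| 48 | 0.630 | 0.794 |
| 72 | 0.500 | 0.707 |
| 168 | 0.198 | 0.445 |

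Both columns fall at every step, so the ranks are identical and rho = 1. The area from a to b is (h / ln 2) × [2^(−a/h) − 2^(−b/h)]:
- 0–168 h: 83.3 for the reference, 115.2 for the collar, ratio 1.38.
- 24–168 h: 61.8 and 92.5, ratio 1.50.
- 0 to infinity: 103.9 and 207.7, ratio 2.00.

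A pure scale error does the same: multiplying every collar value by 0.5 halves the area and leaves rho at 1.

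**2. Graves curves at 6, 24, 48 and 72 h.** Here uptake rises before it falls. Six assumed pairs were tried (uptake half-times 2–10 h, clearance half-lives 40–150 h). Scaling by 0.5 again gave rho = 1.0. Errors of shape gave rho from 0.8 down to −0.2, and rho did not follow the size of the area error: rho was 0.8 both when the collar's area was 0.96 of the reference and when it was 0.48.

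**3. Pooling in Group II.** Simulate 5 patients × 4 times (24, 48, 72, 168 h). Collar and reference curves are drawn independently, so the collar carries no information about the patient. Assumptions: median half-life 72 h with log-SD 0.3, no measurement noise, 20,000 runs per row.

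| Amplitude log-SD (assumed) | Median pooled rho | Share of runs with rho above 0.444 |
|---|---|---|
| 0.3 | 0.68 | 88% |
| 0.5 | 0.55 | 65% |
| 0.75 | 0.41 | 46% |
| 1.0 | 0.31 | 36% |

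The value 0.444 is the nominal 5% point for 20 independent pairs. It serves only as a yardstick, since the protocol plans no test.

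**4. One value per patient at 24 h (n = 5).** In a separate simulation (median half-life 60 h, 10% noise), unrelated curves gave a mean rho of about 0, with 5th to 95th percentiles of −0.8 to 0.8. A collar reading uniformly 50% low gave a mean rho of 0.90. Taken across patients, rho is no longer inflated by time, but it is very imprecise and still blind to scale.

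**The case against.** Several stronger readings are tempting, and the protocol does not support them.

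- A reader might infer that Spearman is the only comparison planned. It is not: the sentence before it promises accuracy and precision by group, and accuracy implies a reference. What is missing is an estimator, and an SAP that is not shown could supply one. That answers the omission only in part, because the protocol itself selects Spearman for the collar-to-reference relationship.
- A reader might infer that rho is near 1 for any two decaying curves. That holds within a patient when both series fall throughout the sampled times. It does not hold in general for Graves curves, or for pooled or one-value-per-patient analyses.
- A reader might infer that a useless collar would pass. The protocol sets no alpha, threshold or test, so nothing is formally passed. The inflation from pooling is real, but its size depends on an amplitude spread that the protocol does not give.
- The 2-fold area error applies only to infinity; over the observed week it is about 1.4-fold.

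It is also fair to say that this is a ten-patient exploratory study and that Drugs/Substances/Devices rules out basing treatment decisions on the collar. That lowers the urgency. It does not make a rank correlation an answer to a question about agreement.

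**Conclusion.** The point stands in this limited form: device accuracy and precision have no estimator, and the only named method relating collar to reference cannot supply them. The blindness to scale follows from the definition of ranks and needs no assumption. The illustrative sizes do rest on assumptions. An error in integrated activity of about 1.4-fold over 0–168 h (2-fold to infinity) at rho = 1 assumes mono-exponential clearance with half-lives of 3 and 6 days. A median pooled rho of about 0.7 to 0.3 for unrelated curves assumes amplitude log-SDs of 0.3 to 1.0 in the Group II design. Spearman therefore cannot support the curve and dose comparisons in the Abstract or the validation wording in the Secondary Objectives. This should be fixed, but it is not critical: the study is an exploratory pilot and no participant's dose depends on the result.

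**What to change.** Amend Study Statistics as follows.

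1. State how collar counts per second are converted to activity or percent uptake, using the background and phantom readings already planned before dosing. Put collar and reference on the same decay basis.
2. Make the main comparison the per-patient log ratio of collar to reference at each paired time. The reference is probe uptake in Group I(A), which has no SPECT, and quantified SPECT in Groups I(B) and II. Leave out the 0 h background reading, where a ratio has no meaning.
3. Where there is SPECT, add the per-patient log ratio of time-integrated activity, over a stated interval and with any extrapolation rule given.
4. Report the mean ratio and 95% limits of agreement by group, with the patient as the unit and a method that allows for repeated measures. Tie the promised accuracy to the mean ratio and precision to its spread.
5. Keep Spearman as descriptive only, across patients at a single named time.
6. In the Secondary Objectives, replace the claim to validate with estimating agreement.

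The cost is protocol wording and modest analysis work, with no added visits or scans. The drawback is that the limits will be very wide. With one value per patient and n = 5, the half-width of the 95% CI for each limit is t(0.975, 4) × √(1/5 + 1.96²/8) = 2.776 × 0.825 = 2.29 SD, which is larger than the 1.96 SD distance from the mean to the limit. The resulting claim is less favourable than a high rho, but it is what five patients per group can support.
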